### Sample size

Based on previous literature, we estimate an effect size of 0.25. The G*Power V.3.1.9.7 software^48^ was employed to determine the requisite sample size. Assuming that the probability of error does not exceed α=0.05 and that the power (1−β) is at least 0.95, an analysis of variance with three groups and two time points with N=66 subjects can demonstrate an effect size of 0.25. Based on previous research projects, we calculate a drop-out rate of 20%, which increases the total sample size to N=82.

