### Statistical analysis

All characteristics collected in the study are described in detail using descriptive methods. Qualitative characteristics are indicated by absolute and relative frequencies. Quantitative characteristics are described using mean values, SD, median, minimum and maximum. Parametric analysis methods are used to evaluate the primary and secondary target variables. If assumptions for parametric tests are violated, appropriate non-parametric alternatives will be considered.

Situational anxiety as the primary outcome (measured using the STAI-state) is analysed using separate 3×2 mixed factorial analyses of variance (ANOVAs) for each of the two chemotherapy sessions, with the between-subject factor ‘intervention’ (VR vs music vs control) and the within-subject factors ‘time’ (before vs after intervention). A probability of error of α=0.05 is set. The unit of analysis is individual patients. Effect sizes will be reported using partial eta squared (η²) for ANOVA analyses. Cohen’s d is calculated for post-hoc comparisons when appropriate. The secondary outcome criteria are analysed exploratively, also using ANOVAs and post hoc tests as appropriate. There is no adjustment of the probability of error. The statistical analysis is carried out with the help of standard statistical software (SPSS V.29). Participants will be included in the statistical analysis if they have completed both assessment time points and received the intervention for a minimum of 10 min per session. Furthermore, the intervention must be administered in consecutive sessions as scheduled. Participants who do not meet these criteria will be classified as dropouts. Both an intention-to-treat analysis and a per-protocol analysis will be performed. The results will be compared and discussed.

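### The stated before/after ANOVA per session cannot include patients who leave before session 2, so the promised intention-to-treat versus per-protocol comparison cannot show bias from their loss

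*Protocol article*

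**What the plan says.** Under Statistical analysis, the primary outcome (STAI-state) "is analysed using separate 3×2 mixed factorial analyses of variance (ANOVAs) for each of the two chemotherapy sessions", with arm as the between-subject factor and "the within-subject factors ‘time’ (before vs after intervention") as the within-subject factor.

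The same section sets an inclusion rule: "Participants will be included in the statistical analysis if they have completed both assessment time points", had at least 10 minutes of intervention per session and were treated in consecutive sessions. "Participants who do not meet these criteria will be classified as dropouts". It then adds: "Both an intention-to-treat analysis and a per-protocol analysis will be performed", and says that the results will be compared and discussed. It does not say which patients form the intention-to-treat set, or how a patient without an after-score enters it.

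Under Sample size, "we calculate a drop-out rate of 20" per cent, which takes 66 patients to 82.

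**The concern.** An intention-to-treat analysis is promised beside a per-protocol one so that the reader can see whether losing patients changed the answer. That works only if the model can use patients with incomplete data. Suppose the intention-to-treat set is read generously as all randomised patients. The stated ANOVA still removes each patient who lacks one of the two scores of a session. For a patient who leaves between T1 and T2, both analyses of session 2 are then blind in the same way.

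Outcome-related loss is plausible on the article's own account. Risk to patients names cybersickness, raised stress or anxiety and a feeling of loss of control, particularly with VR. Sample ends participation for physical weakness, acute side effects or disease progression. Patients also know their arm from T1 onward. If those who leave an active arm before T2 responded poorly at T1, the session-2 contrast among completers is tilted, and nothing in the stated plan would show it.

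**Working it through.** **The plan's own figures.** Inputs from Sample size: effect size 0.25 (read as Cohen's f), three groups, two time points, α = 0.05, power 0.95. The pre-post correlation ρ is not given; 0.5 is assumed.

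- Group × time interaction: λ = f²·N·m/(1−ρ) = 0.0625 × 66 × 2 / 0.5 = 16.5, with 2 and 63 degrees of freedom. Power is 0.953. N = 63 gives 0.944, so 66 is reproduced.
- Drop-out: 66/0.8 = 82.5, against the stated 82. Conversely, 82 × 0.8 = 65.6, so about 16 patients are expected to be lost.

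The planned size therefore already assumes that drop-outs contribute nothing. Power is protected; the issue is bias.

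**What the model does with a missing score.** With two time levels, the arm × time F test equals a one-way ANOVA on D = after − before. If either score is missing, D does not exist and the patient is out of that session's test.

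**Who can enter which analysis**, taking intention-to-treat as all randomised:

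| Type of drop-out | ITT, session 1 | ITT, session 2 | Per-protocol |
|---|---|---|---|
| Under 10 min of intervention, all scores present | yes | yes | no |
| Sessions not consecutive, all scores present | yes | yes | no |
| Leaves after T1 | yes | no | no |
| Stops in T1 before the after-score | no | no | no |

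The two analyses differ in the first two rows, and for session 1 in the third. For session 2, the last two rows are absent from both.

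**Size of the bias.** The article gives no STAI SD and no drop-out pattern, so results are in SD units under assumed patterns: 27 per arm, no true effect, about 20% loss overall.

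*Loss between sessions.* VR and music patients with a poor session-1 change leave before T2 (odds ratio 2 to 4 per SD; loss 20/20/20% or 30/15/15% in VR/music/control). Bias ≈ r × s, where r is the correlation between the two sessions' changes and s is the shift in mean session-1 change among VR stayers.

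- Numerical integration gives s = −0.13 (20% loss, odds ratio 2) to −0.31 (30% loss, odds ratio 4).
- With r = 0.2, 0.2 × 0.13 ≈ 0.03. With r = 0.4, 0.4 × 0.31 ≈ 0.12.
- Simulation gave 0.03 to 0.14 SD in favour of VR. The likelihood-based estimate was off by about 0.01 SD.
- With r = 0 the bias is about zero.

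*Loss within a session.* The after-score is missing more often when the before-score is high (odds ratio 2 to 5 per SD, ρ = 0.5). Bias ≈ (1−ρ) × the difference between arms in how far the before-score mean of stayers has shifted.

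- Loss of 30/15/15%: 0.5 × (0.19 − 0.10) ≈ 0.05, up to 0.5 × (0.34 − 0.18) = 0.08.
- Loss of 40/10/10%: 0.5 × (0.25 − 0.07) = 0.09, up to 0.5 × (0.44 − 0.13) ≈ 0.16.
- Simulation gave 0.05 to 0.16 SD; the likelihood-based estimate was off by at most 0.01 SD. Equal loss gave about zero.
- The direction is against VR. The patients lost are those whose scores would have fallen most by regression to the mean.

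The standard error of the contrast is about 0.30 to 0.32 SD, so the largest bias is about half a standard error (0.16/0.31 ≈ 0.5). Standard errors of the two methods differ by 3% or less.

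**The case against.** The strongest reply is that this rests on silence. A mixed ANOVA needs complete pairs but does not forbid imputing them first. The article is condensed, and missing-data handling is commonly left to an analysis plan, which is not shown here. That stands as far as it goes: the absence of an imputation rule is not the point. The point is that the one primary model the article does fix cannot, as stated, deliver for session 2 the comparison that the article promises.

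A reader might go further and infer that the two analyses rest on nearly the same patients, so that comparing them is empty. The documents do not support that. The drop-out definition is broad: patients with short exposure or non-consecutive sessions can have all four scores, and those lost after T1 have both session-1 scores. For the same reason, the share missing from any one ANOVA may be well below 20%.

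A reader might also expect heavy loss between the before- and after-scores of a session. Recruitment and participant timeline describes an intervention of about 15 to 20 minutes with a team member present, and Data monitoring and management describes supervised questionnaires. Nothing in the article supports 30 to 40% loss in VR at that point.

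Lastly, larger biases can be produced: −0.18 to −0.40 SD in favour of VR, with type I error of 0.085 to 0.252, if VR drop-out is tied directly to the patient's own unrecorded change (correlation 0.5 to 0.8). Those patterns are assumptions, and a mixed model would not correct them, so they are no argument for the change proposed here.

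**Conclusion.** The point holds in a limited form. The stated model excludes patients who leave before T2 from the session-2 test under both labels, so bias from that loss stays invisible. The bias is a risk, not a certainty: modest, at most about half a standard error, and of either sign depending on the mechanism. The loss between sessions is the more plausible route, and it favours VR. The drop-out patterns, the odds ratios and the correlations are all assumed; none comes from the article. Sample size and power are not affected. This is a worthwhile, inexpensive improvement to the plan and not a flaw that invalidates the trial.

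**What to change.** Define the intention-to-treat analysis as one linear mixed model on all available STAI-state scores (before and after, at T1 and T2) from all randomised patients with at least one score, analysed as randomised. Include arm, occasion and arm × occasion, with an unstructured covariance across the four occasions, and test the within-session arm × before/after contrasts from it. Apply the completion, 10-minute and consecutive-session rules, and the ANOVA, to the per-protocol analysis only.

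The model assumes that drop-out depends only on observed scores. It does not correct for patients who stop because of distress during the intervention that was never recorded. Add a simple sensitivity analysis for that case, such as shifting the missing after-scores in the active arms upward over a stated range and reporting where the conclusion changes.

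The cost is a change of wording. The model is available in the SPSS version that the article names, and no new data, visits or patients are needed.

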### Protocol amendments

Protocol amendments were requested initially on 4 November 2022 to extend the sample due to a lack of subjects matching the inclusion criteria. Before the amendment, participants consisted solely of patients with a gynaecological or senological diagnosis. After the amendment, participants with gastrointestinal and haematological diagnoses were also included. To improve the homogeneity of the sample, the GAD-7 with its cut-off criterion of a value ≥5 was introduced as a screening tool. These protocol amendments were granted on 19 November 2022.

A second request to amend the protocol was issued on 3 August 2023 to introduce a self-constructed screening questionnaire for further inquiry into reasons why patients may be disinterested in participation in the study. This protocol amendment was granted on 9 August 2023. All amendments are reflected in protocol version #4, dated 17 March 2025.

### Ethics and dissemination

The ethics committee of the medical faculty of Heinrich-Heine-University Düsseldorf has been obtained (2022-1880). Divergences or modifications of the study protocol will be documented and relevant cases will be reported to the ethics committee. The trial is registered at the German Clinical Trials Register (DRKS00029738), dated 16 August 2022. For all processed data adherence to data protection regulations is warranted. Written informed consent is obtained from patients by the study team and patients are informed that they can withdraw their consent without explanation at any time without facing any consequences. Further, patients are informed that all stored personal data can be deleted on demand at any point. All personal identifiers will be pseudonymised. The final data set can be assessed only by the study team. After the end of the study, the ethics committee will be informed within 90 days.

Findings of the trial will be reported by publishing in international scientific, peer-reviewed journals. Given several outcome parameters, several publications are planned. Further, presentations at conferences are planned. Until publication, the study team commits to full disclosure of the trial results.

### Patient and public involvement

Patients and the public were not involved in the design, conduct or reporting of this study. The research questions, study design, outcome measures, recruitment strategies and dissemination plans were developed by the research team without direct input from patients, carers or members of the public. This decision was made based on the specific nature and feasibility constraints of the study.
